### Data management

#### Confidentiality

Only the principal investigator and her trained and designated research personnel will have access to confidential information. All confidential information that includes personally identifiable information will be coded with a study identification number. The principal investigator and study coordinator(s) will be the only individuals with access to the key of the assigned identification numbers. All confidential information will be locked in a cabinet in a secured location at the University of Maryland School of Nursing or in a database hosted on University of Maryland Baltimore-hosted HIPAA-compliant servers accessible only with a personal password. Personally identifiable information will not be used for this study’s analyses. Everyone using study information will work to keep personal information confidential, and personal information will not be given out unless required by law.

#### Data organization and cleaning

Data will be entered into REDCap electronic forms and electronically collated in a HIPAA-compliant REDCap database managed by University of Maryland Baltimore. Data collected from the myCircadianClock app will be checked in to the Salk Institute. After collation, data will be audited electronically and visually, as needed, for errors.

Whenever possible, cleaning of data from questionnaires, actigraphs, glucose monitors, and other variables will be performed by a blinded researcher. Appropriate graphical or statistical diagnostics methods will be employed in each of the analyses to evaluate distribution of variables (e.g., to identify shape of the distribution and outliers) and also to evaluate the model assumptions (e.g., if deviation from the statistical assumptions is found, we will use alternative methods such as transformations [62] or nonparametric analyses [63, 64]). Outliers will be investigated to determine if they are due to error. If not, analyses will be conducted with and without them to assess sensitivity. Unless stated otherwise, all hypothesis testing will be at the two-sided 0.05 level for type I error as appropriate for phase II trials. SAS, Mplus, and/or JMP will be used for the analyses. Following the intent-to-treat principle, all randomized survivors will be analyzed in the arm as allocated, regardless of their compliance with the intervention or restricted eating contamination in the control group.

In regard to missing data, every effort will be made to facilitate participants’ completion of questionnaires and provision of device data. However, some missing data are inevitable. The reasons for missing data will be recorded and tabulated according to treatment group. If more than 5% missing is observed, missingness mechanism and patterns will be conducted and appropriate approaches employed to minimize the biased estimation. If the missing appears to be *missing at random* [65], we will use multiple imputation or the maximum likelihood method to obtain unbiased estimates of key statistics. If data are suspected to be *missing not at random*, a sensitivity analysis using selection and pattern mixture models will be run to determine the impact on results [66]. If the estimates are similar to the ones obtained from the simpler analysis of only complete cases, we will report the complete-case analysis results [67].

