### Statistical analysis

#### Sample size and power calculation

The protocol is approved to recruit 96 participants. They will be randomized in a 1:1 ratio, intervention: control (48:48) using computer-generated block randomization with blocks of 2 or 4. The estimated attrition is approximately 20%, thus the estimated retention rate is 76 (38:38) evaluable participants. This sample size is appropriate for phase II randomized studies and it will allow us to obtain preliminary estimates of descriptive statistics [mean, standard deviation (SD), confidence intervals (CI), and correlations between repeated measures] [68]. The primary endpoint is the change in fatigue as measured by the MFSI [39] from baseline (T1) to 12 weeks (T3), with a midpoint assessment at 6 weeks (T2). The sample size calculation was based on repeated measure analysis of variance (ANOVA). Assuming correlations [69] of 0.60 between repeated MFSI measurements, a total sample size of *n* = 76 will provide 80% power at the 0.05 two-sided significance level to detect a medium effect size (difference in change between groups divided by the baseline SD of the MFSI score) of 0.50 for the intervention effect. The estimate of effect size is based on our feasibility trial and studies with similar interventions. Our feasibility trial [18] yielded an effect size of 0.55 (within-subject, pre- to post-intervention change) using the Functional Assessment of Chronic Illness Therapy-Fatigue (FACIT-F) questionnaire [70], fatigue subscale, which is likely an overestimate of between-group differences. We decided to employ the MFSI instead of the FACIT-F for this study because the MFSI captures multidimensional aspects of fatigue; the FACIT-F captures multidimensional aspects of quality of life including fatigue, therefore the MFSI is a more appropriate construct for a primary outcome of fatigue.

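### The missing-not-at-random sensitivity analysis depends on an undefined suspicion that observed scores cannot settle, so it can stay off while the week-12 fatigue effect is biased

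*Protocol article*

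**What the plan says.** The rule is in the protocol article under Data organization and cleaning, and it works in steps.

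- A gate comes first: "If more than 5% missing is observed, missingness mechanism and patterns will be conducted".
- If the mechanism looks benign: "If the missing appears to be *missing at random* [65], we will use multiple imputation or the maximum likelihood method".
- If it does not: "If data are suspected to be *missing not at random*, a sensitivity analysis using selection and pattern mixture models will be run".
- A reporting rule closes the sequence: "If the estimates are similar to the ones obtained from the simpler analysis of only complete cases, we will report the complete-case analysis results".

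Read alone, the third step is a plain commitment: "a sensitivity analysis using selection and pattern mixture models will be run to determine the impact on results". The clause in front of it makes it conditional.

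The same paragraph commits to collecting relevant information: "The reasons for missing data will be recorded and tabulated according to treatment group". It does not say how that table bears on the choice between the two branches.

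Under Sample size and power calculation the article states "The estimated attrition is approximately 20" per cent, taking 96 randomized participants to 76 evaluable. The 5% gate will therefore very probably be passed, and the suspicion clause then decides whether any missing-not-at-random analysis is run.

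**The concern.** Missing at random and missing not at random differ in one respect: whether, given everything observed, dropout still depends on the unseen week-12 score of the Multidimensional Fatigue Symptom Inventory (MFSI). That score is by definition not available, and any observed pattern fits both mechanisms. A sensitivity analysis is needed because the assumption cannot be tested. Making it wait for evidence against the assumption weakens its purpose.

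Informative dropout is plausible here. Participants are not blinded (Procedures), the primary outcome is self-reported fatigue (Fatigue), and only one arm carries an eating-window restriction. If TRE participants who are doing worse than expected tend to leave, a missing-at-random analysis favours TRE. The estimates are meant to feed the planning of later trials (Data analysis), so an inflated effect would carry forward.

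**Working it through.** **Inputs from the article.** 96 randomized, 48 per arm; about 20% attrition; correlation 0.60 between repeated MFSI scores; effect size 0.50 baseline SD; two-sided 0.05; three visits (baseline, weeks 6 and 12).

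**The plan's own figures.** 96 × 0.80 = 76.8, which agrees with 76. For the mean of weeks 6 and 12 minus baseline, the variance is (1 + 0.60)/2 + 1 − 2 × 0.60 = 0.60 (SD 0.775). This gives n per arm = 2 × (1.960 + 0.842)² × 0.60 / 0.50² = 37.7, so 38. The stated n = 76 reproduces on that contrast. These inputs are used only as a scale for the bias.

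**Bias for a given departure.** Let p be the fraction missing in an arm, and δ the amount (in SD) by which its unseen scores are worse than missing-at-random predicts. The bias in favour of TRE is p_T·δ_T − p_C·δ_C. The shifts below are assumptions.

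| Missing TRE / control | δ in TRE | δ in control | Bias (SD) | Share of 0.50 |
|---|---|---|---|---|
| 20% / 20% | 0.25 | 0 | 0.05 | 10% |
| 20% / 20% | 0.50 | 0 | 0.10 | 20% |
| 20% / 20% | 1.00 | 0 | 0.20 | 40% |
| 20% / 20% | 0.50 | 0.50 | 0 | 0% |
| 30% / 10% | 0.50 | 0 | 0.15 | 30% |

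**Bias for a given dropout mechanism.** Simulation with 48 per arm, equal correlations of 0.60, 20% missing at week 12 in each arm, earlier visits complete and no true effect. The strength of dependence is assumed.

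| Dropout mechanism | Bias towards TRE (SD) |
|---|---|
| Completely random | 0 |
| Not at random, equally in both arms | 0 |
| TRE only, on the week-12 score, odds ×1.6 per SD | about 0.05 |
| TRE only, on the week-12 score, odds ×2.7 per SD | about 0.10 |
| TRE only, on the part of the week-12 score not predicted by earlier visits, odds ×2.7 per SD | about 0.12 |
| The same, slope 1.2 (odds ×3.3) per SD | about 0.14 |

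A first-order check is bias ≈ slope × residual variance × fraction missing. The residual variance of week 12 given the two earlier visits is 1 − 2 × 0.36/1.6 = 0.55. For odds ×1.6, ln 1.6 = 0.47, and 0.47 × 0.55 × 0.20 = 0.05. For odds ×2.7 (slope about 1.0), 1.0 × 0.55 × 0.20 = 0.11. The simulated 0.10 is a little lower, as expected from the curvature of the logistic function.

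**Can observed scores reveal it?** As an illustration only, take a 5%-level check of whether dropout is related to arm, baseline and week-6 MFSI. It fires in about 5.5% of trials when missingness is completely random. In the TRE-only scenarios it fires in roughly 5% to 14% (22% in one scenario once arm interactions are added). It fires in 87% when missingness is at random through the week-6 score, where the missing-at-random estimate is essentially unbiased (0.01 SD).

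**Does agreement with complete cases help?** With slope 1.2 on the unpredicted part, the missing-at-random and complete-case estimates were both −0.143 SD under no effect, and −0.649 and −0.651 under a true effect of −0.50. They agree and are equally biased, so similarity of these two gives no reassurance about non-random missingness.

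**The case against.** The text does not say that suspicion must arise from the observed scores. A reader might infer that it does, but the article leaves the source open and commits to tabulating reasons by arm. Check-ins about every two weeks give staff a route to learn them. A recorded reason such as the diet not helping would be a fair ground for suspicion. This stands. Reasons may, however, be absent or vague, they do not identify the mechanism, and nothing says which reasons in which arm would turn the analysis on.

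The illustrative check is not in the protocol, so its firing rates do not describe this trial's rule. That also stands. They show only what observed scores can reveal.

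A reader might take 0.14 SD as the expected bias. It is not: it needs strong dropout, in the TRE arm only, driven by the part of the week-12 score that earlier visits do not predict. The biases are also below one standard error of the week-12 contrast. With 38 per arm that is √(2 × 0.64/38) = 0.18 for a baseline-adjusted comparison and √(2 × 0.80/38) = 0.21 for a change score.

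Finally, this is a phase II trial seeking initial estimates, its primary model is reasonable, and a separate analysis plan may define suspicion. That lowers the weight of the point but does not remove it, because the condition itself is written into the article.

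**Conclusion.** The point holds as a rule that is fixed badly, not as missing detail. Whether any missing-not-at-random analysis is reported rests on an undefined judgement that observed scores cannot settle and that the recorded reasons inform only in part.

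The bias that could go unexamined runs from 0 to about 0.14 SD in the scenarios simulated, or 0% to 28% of the 0.50-SD design effect (0.14/0.50). The size rests on assumed dropout strengths, 20% missing in each arm and correlation 0.60. The article gives no figure for the departure, and larger shifts or unequal attrition would widen the range.

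The documents do not support the inference that the safeguard will stay off, that the effect will be biased, or that the plan contains no check at all. It names selection and pattern-mixture models and tabulates reasons by arm. The supported claim is that those models can go unused when they are needed. This is a worthwhile, inexpensive improvement and not a threat to the design.

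**What to change.** Remove the condition. Keep the likelihood-based linear mixed model as the primary analysis. State that a delta-adjusted pattern-mixture analysis of the week-12 MFSI difference will always be reported, whatever the apparent mechanism. Vary the shifts by arm over a range stated in advance, up to the point where the conclusion changes. Worsening only the TRE arm from 0 to 0.5 SD is one possible grid among several. The documents do not determine the range, so the team should choose and justify it before outcomes are analysed. Use the table of reasons by arm to interpret that range, not to decide whether the analysis is run. Agreement with complete cases should not replace the mixed-model result or the sensitivity analysis.

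The cost is a short change of wording, a few extra model runs and one more table. The article already names the method. It expects recruitment to run through 2027, so there is time to make the change before the outcome data are analysed.

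### The reported analysis switches to complete cases whenever the results look similar, with no threshold set; this sits badly with analysing all randomised participants and can carry a modest bias

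*Protocol article*

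**What the plan says.** Data organization and cleaning sets an intent-to-treat rule: "all randomized survivors will be analyzed in the arm as allocated, regardless of their compliance with the intervention". The next paragraph deals with missing data. Above 5% missing, the pattern of missingness is examined. Multiple imputation or maximum likelihood is used if the data appear missing at random, and selection and pattern-mixture models if they are suspected not to be. The paragraph then closes with the reporting rule: "If the estimates are similar to the ones obtained from the simpler analysis of only complete cases, we will report the complete-case analysis results".

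Sample size and power calculation expects losses well above that 5% trigger: "The estimated attrition is approximately 20%, thus the estimated retention rate is 76 (38:38) evaluable participants".

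Data analysis names the primary model as a linear mixed model of MFSI score at baseline, 6 and 12 weeks, with participant as a random effect.

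**The concern.** The rule decides which analysis is reported by comparing two sets of results. The article gives no scale, margin or judge for the comparison, so two analysts with the same data could report different primary results and both be following the plan.

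The default also runs the wrong way. If an analysis of all available data and a complete-case analysis agree, that is a reason to report the first and cite the second as support. Here agreement promotes the analysis that uses fewer participants and needs the stronger assumption about why data are missing.

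Participants know their arm, fatigue is self-reported, and only one arm restricts eating times. Dropout that differs by arm and follows how fatigue is going is therefore plausible, though the article does not predict it. The resulting estimate is intended for planning a phase III trial, where even a modest bias carries forward.

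**Working it through.** **1. How many participants are affected.** Inputs from Sample size and power calculation: 96 randomised (48:48), about 20% attrition.

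- 96 × (1 − 0.20) = 76.8, which the article states as 76 (38:38). The figure reproduces.
- 96 − 76 = 20, and 20/96 = 20.8%.
- The 5% trigger is 0.05 × 96 = 4.8 participants, so at planned attrition the missing-data paragraph will apply.

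The 20 is a planned figure. It would be larger if *complete* means all three visits and some participants miss only week 6.

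**2. What is discarded.** A likelihood-fitted mixed model keeps a participant who has baseline and week-6 scores but no week-12 score. A complete-case analysis does not.

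**3. Size of the bias (illustrative).** From the article: 48 per arm, correlation 0.60 between visits, target effect 0.50 baseline SD. The rest is assumed:

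- no true effect, unit SD, equal correlations between visits;
- control dropout: logit P = −2, that is 1/(1 + e²) = 12%, at random;
- TRE dropout: logit P = −0.95 + b × (week 6 − baseline), with b = 0.8 (mild, 30% dropout) or b = 1.5 (strong, 33%);
- overall dropout is then (12 + 30)/2 = 21% or (12 + 33)/2 = 22.5%, close to plan.

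For each of 20,000 simulated trials per scenario, let CC be the complete-case difference in change and ML the likelihood estimate from all 96. The rule is taken as: report CC if |CC − ML| < c, otherwise report ML. The article does not state the second half, and c is not given, so a range is shown. Negative values favour TRE.

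- Always CC: bias −0.087 SD (mild), −0.147 SD (strong).
- Always ML: about 0 in both.

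| c (SD) | Bias of the rule, across the two scenarios (SD) | As % of 0.50 |
|---|---|---|
| 0.05 | about 0 to −0.004 | under 1% |
| 0.10 | −0.014 to −0.027 | 3 to 5% |
| 0.15 | −0.045 to −0.055 | 9 to 11% |
| 0.20 | −0.07 to −0.08 | 14 to 16% |

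The rule selects CC in 29% (mild) and 10% (strong) of trials at c = 0.05, in 62% and 30% at c = 0.10, and in about 94% and 75% at c = 0.20.

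Agreement is a weak check. Among trials within 0.10 SD, CC still averages −0.056 (mild) and −0.101 SD (strong).

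**4. Other dropout patterns.** A separate set of 4,000 runs per scenario used dropout slopes of 1 logit per SD of early change.

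- Same direction in both arms: CC bias is about 0.
- One arm only: about 0.09 SD.
- Opposite directions: about 0.18 SD.
- Completely random at 20%: no bias. The standard error is about 0.205 to 0.208 SD for CC against about 0.200 to 0.202 SD for ML. Taking 0.205 and 0.200, the variance ratio is (0.205/0.200)² = 1.05.

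**The case against.** The strongest reply is that the rule limits itself. Complete case is reported only when it agrees with the missing-data analysis, so a large discrepancy should never reach the reader. That largely stands. A reader might infer that the reported effect would carry the full 0.09 to 0.15 SD bias. That figure belongs to a plan that always reports complete case, which this one does not. The rule's own bias is smaller at every cut-off tried, and near zero at a strict one.

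The dropout scenario is also assumed. The article plans equal retention (38:38), and the control is matched for time, attention and expectancy. This stands as a limit on the size, not on the defect.

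Three further inferences go beyond the text:

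- That a fifth of participants will be dropped. The loss follows only if the estimates are judged similar, and 20% is planned attrition. Power was set on 76, so the loss creates no shortfall against the stated power basis.
- That the rule flatly breaks intent-to-treat. The sentence mainly concerns allocation, compliance and contamination, with missing outcomes handled separately. The conflict is with its wording that all randomised survivors are analysed; it is not a reclassification by adherence.
- That similarity is judged by someone who knows the arms. The article does not say who judges it or whether labels are masked. The objection needs only that both results are known.

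The conditional use of missing-not-at-random models is no fault on this text. They are triggered by suspicion and called a sensitivity analysis; running them always would be a preference.

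**Conclusion.** The concern holds as a badly fixed reporting rule with moderate consequences. The sentence lets the results select the reported analysis against an undefined standard. When it fires at planned attrition, about 20 of 96 randomised participants and their usable early data leave the reported result.

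Under the assumed one-directional dropout, the bias runs from about 0 to 0.03 SD for cut-offs of 0.05 to 0.10 SD, and from about 0.05 to 0.08 SD for cut-offs of 0.15 to 0.20 SD, towards TRE. The near-zero bias of the likelihood analysis rests on dropout depending only on observed scores. The article gives no MFSI standard deviation, so these sizes cannot be set against the 4.5-point minimal clinically important difference.

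The rule has no offsetting benefit: with random dropout it gains nothing and loses a little precision. It should be fixed, but it does not undermine the trial's design.

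**What to change.** Delete the sentence that makes complete case the reported result. State instead that the linear mixed model already planned under Data analysis, fitted by maximum likelihood to all randomised participants with any MFSI data, is the reported primary analysis whether or not it agrees with complete case. Report complete case only as a labelled sensitivity analysis.

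This changes wording in the protocol and any analysis plan. It needs no new data, no change in sample size and no new model. The article expects recruitment through 2027, so the change can be made before outcome results are seen.

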### Statistical analysis

#### Sample size and power calculation

The protocol is approved to recruit 96 participants. They will be randomized in a 1:1 ratio, intervention: control (48:48) using computer-generated block randomization with blocks of 2 or 4. The estimated attrition is approximately 20%, thus the estimated retention rate is 76 (38:38) evaluable participants. This sample size is appropriate for phase II randomized studies and it will allow us to obtain preliminary estimates of descriptive statistics [mean, standard deviation (SD), confidence intervals (CI), and correlations between repeated measures] [68]. The primary endpoint is the change in fatigue as measured by the MFSI [39] from baseline (T1) to 12 weeks (T3), with a midpoint assessment at 6 weeks (T2). The sample size calculation was based on repeated measure analysis of variance (ANOVA). Assuming correlations [69] of 0.60 between repeated MFSI measurements, a total sample size of *n* = 76 will provide 80% power at the 0.05 two-sided significance level to detect a medium effect size (difference in change between groups divided by the baseline SD of the MFSI score) of 0.50 for the intervention effect. The estimate of effect size is based on our feasibility trial and studies with similar interventions. Our feasibility trial [18] yielded an effect size of 0.55 (within-subject, pre- to post-intervention change) using the Functional Assessment of Chronic Illness Therapy-Fatigue (FACIT-F) questionnaire [70], fatigue subscale, which is likely an overestimate of between-group differences. We decided to employ the MFSI instead of the FACIT-F for this study because the MFSI captures multidimensional aspects of fatigue; the FACIT-F captures multidimensional aspects of quality of life including fatigue, therefore the MFSI is a more appropriate construct for a primary outcome of fatigue.

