#### Data analysis

Prior to hypothesis testing, the demographics and patients’ characteristics will be compared between TRE vs. control groups and the relevant variables (e.g., age) that differ by group will be included as confounders in hypotheses testing. To provide estimates of efficacy comparing TRE vs. an unrestricted eating pattern to alleviate fatigue, the first objective is to longitudinally evaluate the between-arm difference in mean change in MFSI score from baseline to post-intervention (12 weeks after baseline) in a linear mixed model. A data collection point at 6 weeks is also included in order to capture any effects of the intervention at a shorter time point. The outcome will be MFSI score and the fixed effects will include arm (TRE vs. control), time (baseline, 6, and 12 weeks), and interactions between arm and time. Statistical significance of the arm×time interaction will be assessed at an alpha of 0.05. Participants will be included as a random effect accommodating the correlations between repeated measures. If any aforementioned potential confounders (e.g., age, body mass index, psychological symptoms, time since completion of treatment) are not evenly distributed between the two groups, they will be added to the model. The results of the analyses together with the estimates of distribution parameters (e.g., mean, SD) of MFSI values as well as the change scores will be used in planning future randomized trials. In addition to statistical significance, we will assess the effect sizes and whether any changes seen are clinically meaningful. The MFSI has a published MCID of 4.5 points [49].

A second objective is to assess the sustainability of TRE three months after the intervention. At 24 weeks, follow-up will occur with several questionnaires. Participants will be asked to self-report the time of their typical first food/beverage intake and their typical last food/beverage intake at night over the previous week. The eating window will be calculated, and its length will be compared between arms using a t-test. We will also evaluate the proportion of patients adhering to 10-h window. We hypothesize those in the intervention group will have adopted a significantly shorter eating window than those in the control group.

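### The stated 80% power does not apply to the stated primary endpoint: the protocol's own inputs give about 67% for the baseline-to-week-12 change

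*Protocol article*

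**What the plan says.** The section Sample size and power calculation fixes every input. Ninety-six participants are randomised 1:1 and about 20% are expected to drop out, "thus the estimated retention rate is 76 (38:38) evaluable participants". The primary endpoint is the MFSI change from baseline (T1) to 12 weeks (T3); week 6 (T2) is described as a midpoint assessment. The calculation is attributed to repeated-measures ANOVA, without naming the contrast. The correlation is given as "Assuming correlations [69] of 0.60 between repeated MFSI measurements", and the effect size as "difference in change between groups divided by the baseline SD of the MFSI score) of 0.50 for the intervention effect". From these the section concludes that the sample "will provide 80% power at the 0.05 two-sided significance level to detect a medium effect size".

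The Data analysis section repeats the target, the between-arm difference in mean change from baseline to week 12. It specifies a linear mixed model with arm, time (baseline, 6 and 12 weeks) and their interaction as fixed effects. Baseline is one of the outcome times, not a covariate. The test is given as follows: "Statistical significance of the arm×time interaction will be assessed at an alpha of 0.05".

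**The concern.** The article states an endpoint, a test, a full set of inputs and a power figure, and these do not agree. With a correlation of 0.60, a change score has an SD only slightly below the baseline SD, so 0.50 baseline SD is not a large enough standardised effect for 38 per arm to reach 80%.

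The figure matters because the trial plans a significance test at 0.05, and its Discussion says the results will give clinicians evidence for or against including nutrient timing in their teaching. A null result would be read against the advertised 80%.

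There is also little slack in the target. The article calls the single-arm pilot effect of 0.55 a likely overestimate of a between-group difference, yet plans for 0.50 against an active control matched for time, attention and expectancy.

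**Working it through.** **Inputs**, all from Sample size and power calculation: 38 per arm; two-sided alpha 0.05; correlation r = 0.60; difference in change of 0.50 baseline SD. Two assumptions are added: the SD is the same at every visit (set to 1), and the correlation is the same between every pair of visits.

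For a contrast with standard deviation s, the noncentrality is 0.50 / (s × sqrt(2/38)), with sqrt(2/38) = 0.2294. Power comes from the noncentral t distribution with 74 df. Figures with the mixed model's 2 × 74 = 148 df are given where they help.

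**1. Reproducing the 80%.** Take the mean of weeks 6 and 12 minus baseline, with the full 0.50 at both visits.
- Variance = (1 + r)/2 + 1 − 2r = 0.80 + 1 − 1.20 = 0.60, so s = 0.775.
- Noncentrality = 0.50 / (0.775 × 0.2294) = 2.81.
- Power = 79.3% (74 df), 79.8% (148 df) or 80.3% (normal approximation). The normal formula asks for exactly 38 per arm.

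This matches the stated figure. That the sponsor used this contrast is an inference from the match; the article does not say so.

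**2. The stated endpoint, week 12 minus baseline.**
- Variance = 2(1 − r) = 0.80, so s = 0.894.
- Standardised effect = 0.50 / 0.894 = 0.559.
- Noncentrality = 0.50 / (0.894 × 0.2294) = 2.44.
- Power = 67.2% (74 df), 67.8% (148 df) or 68.3% (normal approximation).

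**3. The stated test, arm by time with three time levels (2 df).** The noncentrality is (76/4) × Σ(d − mean d)² / (1 − r) = 19 × Σ(d − mean d)² / 0.40, referred to F(2, 148).

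| Effect at baseline, week 6, week 12 | Σ(d − mean d)² | Noncentrality | Power |
|---|---|---|---|
| 0, 0.50, 0.50 | 0.1667 | 7.92 | 70.3% |
| 0, 0, 0.50 | 0.1667 | 7.92 | 70.3% |
| 0, 0.25, 0.50 | 0.1250 | 5.94 | 57.0% |

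**4. A baseline-adjusted week-12 comparison** (not the model as written).
- s = sqrt(1 − r²) = sqrt(0.64) = 0.80.
- Noncentrality = 0.50 / (0.80 × 0.2294) = 2.72.
- Power = 76.7%.

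**5. What 80% would take for the week-12 change score.**
- At 76 evaluable: an effect of 0.58 baseline SD, or a correlation of about 0.705.
- At 0.50 SD and r = 0.60: 52 evaluable per arm (104 in total), so 104 / 0.80 = 130 randomised.
- If all 96 completed (48 per arm): 77.4%.

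For the baseline-adjusted contrast at 76 evaluable, 80% power corresponds to 0.52 SD.

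**The case against.** **It is not a slip in arithmetic.** The article says the calculation rests on repeated-measures ANOVA, and one repeated-measures contrast does give 80% at 38 per arm. This stands as a description of how the error probably arose: the contrast that was powered is not the one defined as the endpoint. It does not rescue the figure. That contrast appears nowhere as endpoint or test, and it needs the full effect by week 6. The Discussion says the authors do not know how long the intervention must run to produce clinically meaningful effects. Leaving the contrast to a fuller document would not help either, because the article itself names a different endpoint and test.

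**A complete-case change score is not the planned analysis.** The mixed model would also use partial data from the 20 participants expected to drop out. This is right, and it adds a little. With 48 per arm randomised and 38 completing, the baseline-to-week-12 contrast has about 70% power if dropouts supply baseline only, and about 71% if they also supply week 6. The 2-df test has 73% to 79% with the full effect at both visits, and 59% to 60% if it builds linearly. All remain below 80%, and the article ties its own claim to 76.

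**It is a phase II trial meant to provide initial estimates.** No interim or stopping rule depends on the 80%, and the misstatement neither biases the estimate nor inflates type I error. That limits the harm, but the article still makes a definite power claim alongside a 0.05 test.

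**The 0.50 is disclosed and has a second basis.** The article also cites studies of similar interventions, which cannot be checked here. The remark about the target is therefore context; the power discrepancy does not depend on it.

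**Conclusion.** The concern holds. For the endpoint, sample, correlation and effect that the article states, power is about 67%, or at most about 71% if partial data from dropouts are counted, against a stated 80%. The arm-by-time test has 57% to 70% at 76 evaluable, and a baseline-adjusted contrast 77%. The risk of missing a true effect of 0.50 SD on the stated endpoint is about one in three.

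These figures assume equal SDs and a common correlation of 0.60 across visits. The range for the interaction test also assumes 2 df and the effect profiles shown. The same assumptions reproduce the article's 80% for the averaged contrast, so they are not what causes the gap.

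**What to change.** Name the contrast that will be tested and give its power. Two wordings fit the present sample:

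- *Change score as now defined:* 76 evaluable participants give 67% power for a difference in baseline-to-week-12 change of 0.50 baseline SD, and 80% power for 0.58 SD.
- *Preferred:* make the baseline-adjusted week-12 contrast primary, and state 77% power at 0.50 SD or 80% at 0.52 SD. This is an analysis choice, not the only valid correction, but it recovers most of the shortfall without cost.

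In either case the Data analysis section should name the single week-12 contrast as the primary test, so that the test and the power statement match. If the averaged week 6 and 12 contrast was really intended, the endpoint and test must be rewritten to say so, with the assumption of a full effect by week 6 stated. Holding 80% for the change score at 0.50 SD would instead take about 130 randomised.

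The first two options change only wording in the protocol and analysis plan. Recruitment is expected to run through 2027, so this can be settled before analysis. The cost is a less favourable published figure.
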